**Intervention:** If feasible, an ED-coach (passive or active form) will be appointed to each participant of the care pathway. The NSC will be evaluated in-depth, the patient will undergo APOP-screening during triage and if indicated, a comprehensive geriatric assessment will be performed after discharge from the ED at another department. The patient will be seen by a specialist or experienced resident in training at the ED, who will order a standard set of diagnostic tests and review the results. The APOP-risk score will guide further actions in the care pathway. A verification of the medication list will be performed <24 hours and a review of the medication will follow during admission.

**Control cohort:** Recruitment of controls will occur before implementation of the care pathway and on workdays between Monday – Friday from 11:00 am – 20:00 pm. The study period is estimated at approximately 6 months, according to study protocol. Each participating hospital will inform participants regarding their policy on data collection prior to implementing the care pathway. Data for controls within hospitals with access to CTcue will be collected retrospectively. The other participating hospitals will include eligible patients prospectively for the same estimated study period. After 30 days, the research nurse will evaluate complications that occurred after the patient leaves the care pathway.

**Main study parameters/endpoints:** Main endpoints are to evaluate the length of stay at the ED (ED-LOS) and exploring patient satisfaction on 4 established domains. Secondary objectives are evaluating the length of stay at the hospital (HOSP-LOS), discharge destination, medical diagnosis (at admission versus discharge), frequency of readmissions / revisits, 30-day mortality, loss of functional

status and costs-effectiveness of the care pathway. Study parameters are age, gender, main non-specific complaint, main diagnosis at ED-arrival and discharge, way of arrival (per ambulance, public transportation, etc.), main domain of NSC (somatic, nutrition, psychosocial, functional, mobility, falls), living situation (independent, care at home), diagnostic tests, specialist seeing the patient and consulting specialists and ED-logistics (time of arrival at ED, duration of triage, triage colour).

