## **3. OBJECTIVES**

1. The **primary objectives** of the care pathway are to evaluate:

- Length of stay at the ED (ED-LOS)
- Patient satisfaction on 4 domains

1. relief of symptoms (degree of relief and symptoms, duration until symptom relief, impact on function)
2. understanding the diagnosis and cause of symptoms, understanding prognosis
3. presence and understanding of the diagnostic, therapeutic and follow-up plan
4. reassurance during ED-stay

2. The **secondary objectives** of the care pathway are to evaluate:

- Length of stay at the hospital (HOSP-LOS)
- Discharge destination
- Medical diagnosis (at admission versus discharge)
- Frequency of readmissions / revisits
- 30-day mortality
- Loss of functional status
- Costs-effectiveness of the care pathway

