## 5. STUDY POPULATION

### 5.1.1 Population

Older adult patients presenting with a non-specific main complaint at the practice of their general practitioner (GP) will be screened for inclusion. If a patient meets the inclusion criteria, the GP will refer the patient to a hospital that implemented the care pathway and notify the specialist at the ED (internist, ED-doctor or elderly care physician). Every referring care professional will have a card, which provides information on how to refer a patient to the care pathway and to whom. Patients not referred by the GP can enter the care pathway in several other ways:

- if referred by the practitioner at a nursing home
- if triage at the ED points to a NSC

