### 5.1.2 Inclusion criteria

In order to be eligible to participate in this study, a subject must meet all of the following criteria:

- Indicated for admission to hospital, **and**
- Age  $\geq$  70 years, **and**
- A non-specific main complaint at presentation, such as:—
  1. somatic problems:
    - *weakness*: physical weakness in the body limiting the patient to perform daily activities
    - *not feeling well*: patients expressing a passive behaviour due to not feeling well physically or mentally
    - *change in nutritional status*: an abrupt decline of eating and/or drinking, compared to previous eating habits
    - *unexplained weight loss*: an ongoing weight loss or recent weight loss of more than 10% of baseline in the previous month, not related to a modified diet or exercise
  2. a higher demand of care:

- *loss of independency*: an abrupt or ongoing decline of being able to perform daily activities independently
- *a necessity for a change in the living situation*, due to a higher demand of care
- *a necessity for 24-7 care*, not indicated previously

3. cognitive problems:

- *disorientation*: inability to recall current date, name or current environment
- *changes in behaviour*: unexplained agitation, abrupt changes in behaviour
  - *cognitive decline*: abrupt decline in cognitive performances

4. functional status:

- *loss of mobility*: change in functional status leading to limited mobility

5. unexplained falls: a fall not related to extrinsic factors such as poor lighting, unsafe stairways, and irregular floor surfaces or to a precise medical or drug-induced cause

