  - o Checking adherence to the recommended APOP-guidelines after completion

- 5. Tasks of the nurse:
  - Performing the APOP screening (potential)
  - Conventional care at the ED
  - Performing the ordered diagnostic tests
  - Performing actions following the APOP-risk score
- 6. Tasks of the doctor:
  - Conventional care at the ED
  - Ordering a standard set of diagnostics, at least: ECG, lab, urinalysis, X-thorax and bladder scan.
- 7. Actions following APOP-screening:
  - 1. Low risk, no supplementary actions recommended
  - 2. High risk of functional decline - the following actions are recommended among others; in case of suspected dehydration at presentation: starting early fluid administration, in case of admission: limiting the length of stay at the ED and organizing early transfer to the ward.
  - 3. High risk of cognitive decline - the following actions are recommended among others; Making sure the patient has a comfortable bed, has adequate lightning in the room and knows how to call for help.
  - 4. High risk of functional and cognitive decline - the following actions are recommended among others; consider the diagnosis delirium and an internist geriatric medicine or clinical geriatrician can be consulted for a comprehensive geriatric assessment after discharge from ED.
- 8. Discharge from the ED:
  - Possibilities include: admission to the ward, discharge to home, discharge to facility, discharge to short stay facility for primary care, discharge to geriatric rehabilitation.
  - Each study participant will be followed-up after leaving the care pathway.
  - A review of the medication list will be performed by the doctor at the ward, elderly care physician, the clinical pharmacologist or hospital pharmacist

- 9. Tasks of the research nurse / researcher:

- Collecting data for the database (see study parameters and endpoints)
- Collecting data for each participant 30 days after leaving the care pathway

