## 5.4 STUDY PARAMETERS / ENDPOINTS

### 5.4.1 Main study parameter/endpoint

#### *Baseline characteristics:*

- Age in years
- Gender (male/female)
- Referral category NSC
  - o Somatic
  - o Higher demand of care
  - o Cognitive problems
  - o Functional status
  - o Unexplained falls
- Main diagnosis at ED (DOT/DBC/ICD10)
- Way of arrival (per ambulance, public transportation, own transport, etc.)
- APOP-score
- Adherence to the recommended actions after APOP-screening and risk of functional decline
- Specialist seeing the patient and consulting specialists during ED-stay
- Diagnostic tests (X-ray, EKG, urinalysis, bladder scan and the frailty lab)
- ED-logistics (time of arrival at ED, duration of triage, triage colour, ED loss etc)
- In the case of admission: duration of admission (days) and reason for admission
- Living situation (independent, care at home, etc)
- Zip (postal code)
- Discharge destination (home, facility, care at home)
- Change in medication list after review
- Patient satisfaction

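### Discharge destination is coded as a bare place, with overlapping categories and no stated time point, and is not tied to where the patient lived before, so return to a facility and new placement are merged

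*Protocol*

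**What the plan says.** Section 3 lists "Discharge destination" among the secondary objectives. The only coding is in section 5.4.1: "Discharge destination (home, facility, care at home". The item stands under the baseline characteristics and is absent from the list of endpoints that follows.

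Two lines earlier in the same list is "Living situation (independent, care at home, etc". The Summary has "living situation (independent, care at home". Neither names nursing home.

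Section 5.1.1 admits patients "if referred by the practitioner at a nursing home". Section 5.1.2 accepts "a necessity for a change in the living situation" as a qualifying complaint, and also a new need for round-the-clock care. It further requires that the patient has an indication for hospital admission.

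Section 5.3, item 8, describes the ways of leaving the ED. They include admission to a ward, home and a facility, and also "discharge to short stay facility for primary care, discharge to geriatric rehabilitation".

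Controls are gathered by each hospital before implementation (5.1.5) under the same eligibility criteria (5.1.4). Section 5.5 names chi-square or Fisher's exact test for categorical data. It names GEE to account for similarity within hospitals, and no adjustment for living situation.

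**The concern.** A place of discharge is informative about a care pathway mainly in relation to where the patient came from. Under the stated coding, a nursing-home resident who returns to the nursing home and an independent patient who is newly placed there are both recorded as going to a facility. For a patient enrolled because the living situation has to change, a facility may be the solution to the presenting problem, so the same code carries a third meaning.

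The coding has two further weaknesses. A patient living at home with care fits two of the three categories. And because entry requires an indication for admission, many patients will leave twice, first the ED and then the hospital, while the item does not say which departure is recorded.

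Two things are at stake. The first is sensitivity: returning residents add events that the pathway cannot change. The second is confounding. The comparison is before-after, and cases are found differently in the two periods. Pathway patients come through referral or ED triage. Controls come from an electronic record search or from patient numbers saved by the ED specialist. If the resident share differs as a result, the facility proportion moves although no patient's course has changed.

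**Working it through.** **The plan's own figure.** Discharge destination has no figure of its own. The only calculation is for ED length of stay (5.1.5): a difference of 10% of 3 h 20 min, or 0.333 h, two-sided 5%, power 80%. With the SD read as 1 h 17 min (1.283 h), n = 2 × (1.960 + 0.842)² × (1.283/0.333)² gives 233 per group, 466 in total, as stated. This point does not affect that number. From 5.1.5 I take only the target of 300 per group.

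**Model.** Let r be the share of facility residents, all assumed to return to a facility, and q the proportion of non-residents newly placed. The proportion recorded as going to a facility is p = r + (1 − r) × q. The documents give neither r nor q, so every value below is an assumption.

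**Confounding, no true effect (q = 15% in both periods)**
- Residents 5%: 0.05 + 0.95 × 0.15 = 0.1925.
- Residents 15%: 0.15 + 0.85 × 0.15 = 0.2775.
- Difference 0.085; pooled p = 0.235; SE = √(0.235 × 0.765 × 2/300) = 0.0346.
- z = 0.085/0.0346 = 2.46, p about 0.014.

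**A small shift.** Residents 5% versus 7%: 0.1925 versus 0.07 + 0.93 × 0.15 = 0.2095. The difference is 0.017, SE about 0.0327, z about 0.5. That is negligible.

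**A range.** Probability of a significant result at 300 per group when q is equal in both periods:

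| Residents, control → pathway | q = 10% | q = 20% |
|---|---|---|
| 10% → 10% | 5% | 5% |
| 10% → 15% | 27% | 19% |
| 10% → 20% | 74% | 56% |

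**Dilution, equal resident shares, q falling from 20% to 10%**

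| Residents in both periods | Facility, control vs pathway | Power, bare place | Power, non-residents only |
|---|---|---|---|
| 10% | 28% vs 19% | 74% | 90% (n = 270 per group) |
| 20% | 36% vs 28% | 56% | 87% (n = 240 per group) |

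With equal shares there is no bias. The loss is in power, even though the analysis of non-residents uses fewer patients.

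**The case against.** The strongest reply is that the data needed are largely collected already. Living situation is in the same list as discharge destination, and the referral category has its own level for a higher demand of care. Setting one against the other, or stratifying, is a derived-variable decision that usually belongs in a statistical analysis plan, which is not shown. This stands for the adjustment. It does not stand for the categories or the time point, which are fixed when data are collected. The living-situation item leaves nursing home to an open remainder, and the two items do not share categories. Control data from the record search are retrieved anonymously according to the defined parameters (5.1.4), so a code that merged returns with new placements may not be separable later.

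Second, the bracketed categories may be examples, and item 8 of section 5.3 describes exits from the ED, not a coding scheme. That is fair, and the difference between the two lists is therefore weak evidence of a contradiction. The overlap and the missing time point remain on either reading.

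Third, a reader might infer that the item measures case-mix and not outcome. The documents do not support this. Controls meet the same criteria and each hospital's pathway patients are to be compared with its own controls (5.3.1), so bias needs a shift in the resident share. Nor can it be inferred that the referral card raises that share: the card goes to every referring professional, the general practitioner is the first-named route, and more such referrals could lower it.

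Fourth, the protocol states no hypothesis for this item and does not call facility discharge a bad outcome. That is correct, and it limits the weight of the point.

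**Conclusion.** The point holds as a defect of measurement in a secondary objective. As written, the item overlaps in its categories, has no time point, is not linked to prior residence and is missing from the endpoint list. It merges return to a facility with new placement.

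The cost is certain in kind but unknown in size. If resident shares are equal, the comparison is unbiased but less sensitive: 56% power against 87% with 20% residents, on the assumed fall in placement. If they differ, the unadjusted test can reject without any true effect: 19.3% versus 27.8%, z about 2.5, for residents at 5% versus 15%. At a 2-point shift the effect is negligible. All rates are assumptions, and neither the direction nor the size of a shift follows from the documents.

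A reader might simply add 15 points to each resident share and obtain 20% versus 30%. That is not a null case. Only non-residents can be newly placed, so it implies that their rate rises from 0.15/0.95 = 15.8% to 0.15/0.85 = 17.6%.

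**What to change.** 1. Use one ordered, mutually exclusive list for both living situation before the visit and final destination, for example: independent at home; at home with care; temporary facility or rehabilitation; nursing home or other permanent facility.
2. State the time point: hospital discharge if the patient was admitted, otherwise ED discharge.
3. Define the endpoint as a higher level of care than before the visit and compare that proportion between groups.
4. Move the item from the baseline characteristics to the endpoint list in 5.4.1.
5. Report facility residents, and patients entered in the higher-demand-of-care category, separately.

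The cost is a change in case report form wording, the same categories in the record search for controls, and one derived variable. No new visit or staff is needed. Section 4 describes control inclusion as restarted from August 2020, so controls already collected would have to be recoded from their records where these can still be traced. The downside is that permanent residents cannot worsen on this scale and add no information to the endpoint.

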#### Endpoints are:

- Diagnostic procedures before and after implementation of the care path (quantity)
- ED length of stay – ED-LOS (in hours)
- Hospital length of stay – HOSP-LOS (in days)
- Readmissions in 90 days (yes/no)
- 30-day mortality
- Revisits in 30 days (yes/no)
- Patient satisfaction

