Studies have shown that patients with NSCs have different characteristics compared to patients with specific complaints (SCs) [4]. Patients with NSCs have more comorbidities, use more medications, are at a higher risk of functional decline due to longer hospitalization and have a higher 30-day mortality rate compared to patients with SCs. Undertriage and unnecessary testing often contribute to a prolonged ED stay and frequent readmissions [5]. Furthermore, clinical experience of the health care provider seeing the patient with NSCs impacts diagnostic accuracy [6]. We aim to implement an integrated care pathway in different emergency departments of the Brabant area, focused on streamlining the care of patients with NSCs at the ED. This will be accomplished by evaluating the NSC in-depth (primary care), performing APOP (triage at the ED), screening certain domains of the CGA if a patient is high-risk according to APOP (somatic, nutrition, psychosocial, functional, mobility, falls), performing a standard set of diagnostic tests (at least: ECG, lab, urinalysis, X-thorax and bladder scan) and providing ‘specialized care’, as described in the methods section. In this care pathway, we will guide actions according to the APOP-risk score. After admission, a verification and review of the medication list will be performed. We hypothesize that the care pathway will primarily improve patient satisfaction and reduce the ED-length of stay. Reduced hospital length of stay, decreased 30-day mortality, improved functional status (daily activities, mobility, cognition), a reduction of (re-)admission rates for older adults with NSCs and reduced costs of care for this patient population might follow as a result of implementing this care pathway.

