## 5.5 STATISTICAL ANALYSIS

Primary and secondary study parameters and endpoints are described in 'Study parameters/endpoints'. All statistical analyses will be performed with SPSS 24.0 for Windows (IBS, SPSS Statistics, Chicago, IL, USA). Descriptive statistics will be used for frequencies, percentages, means and standard deviations. Continuous variables will be analysed using independent t-tests, whereas the categorical data will be analysed by chi-square or Fisher's exact test. Median and interquartile ranges of non-normally distributed categorical and metric variables of the study will be

assessed using Mann-Whitey-U-test. Prevalence of the most frequent diagnosis (coded ICD-10) at discharge will be presented in percentages. HR and corresponding 95% confidence intervals will be calculated. Generalized Estimating Equations (GEEs) will be used, which adjust for observations made within the same hospitals being more alike. All tests will be performed using a significance level of  $\alpha = 0.05$ . A two-sided p-value  $< 0.05$  will be considered significant.

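### HOSP-LOS counts days in hospital with no rule for death, so an in-hospital death earlier than survivors' usual stay scores as a short, favourable stay

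*Protocol*

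**What the plan says.** Section 5.4.1 of the protocol lists the endpoint as "Hospital length of stay – HOSP-LOS (in days". The matching data item in the same section is "In the case of admission: duration of admission (days) and reason for admission". The discharge destinations listed there are "Discharge destination (home, facility, care at home"; death is not among them. 30-day mortality is a separate endpoint with no link to the stay.

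Section 5.5 states "Continuous variables will be analysed using independent t-tests". Non-normal variables are to be "assessed using Mann-Whitey-U-test", and GEE is named for similarity within hospitals. The same section says "HR and corresponding 95% confidence intervals will be calculated" but gives no endpoint, event or censoring rule for that hazard ratio.

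Section 2 names "Reduced hospital length of stay, decreased 30-day mortality" together among the benefits that could result from the pathway. It also describes these patients as having higher 30-day mortality than patients with specific complaints, without giving a rate. Section 3 places HOSP-LOS among the secondary objectives.

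**The concern.** A length of stay has two kinds of ending, discharge alive and death. Counted as plain days, a patient who dies on day 2 and one who goes home well on day 2 have the same value, and a shorter stay is read as the better result. The protocol hopes for fewer deaths and shorter stays together, yet under this scoring the two can pull against each other. An averted early death replaces a short stay with a longer one, and an additional early death does the opposite.

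What is at stake is the interpretation of one secondary comparison in patients aged 70 or over whose eligibility includes "Indicated for admission to hospital". How patients who are not admitted in the end are handled is a different question and is not part of this point.

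**Working it through.** **The plan's own figures.** The protocol gives no mean, SD, death rate or effect size for HOSP-LOS, so there is nothing to reproduce for this endpoint. Its one calculated figure, 233 per group in Section 5.1.5, concerns ED-LOS. It reproduces when the SD is read as 1 h 17 min and has no bearing here. The only document input used below is the target of 300 patients per group.

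**Formula.** Let p be the in-hospital death risk, Ls the mean stay of survivors and Ld the mean stay of those who die. Then

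mean HOSP-LOS = (1 − p) × Ls + p × Ld.

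If the pathway changes only p, and patients whose death is averted then stay as long as other survivors, the difference (pathway minus control) is

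shift = (p_control − p_pathway) × (Ls − Ld).

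**Assumed inputs.** Ls = 8 days; Ld = 3 or 4 days for early deaths; deaths averted in 1 to 5% of patients.

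| Deaths averted | Ls | Ld | Shift in mean (days) |
|---|---|---|---|
| 1% | 8 | 4 | 0.01 × 4 = +0.04 |
| 2% | 8 | 4 | 0.02 × 4 = +0.08 |
| 3% | 8 | 3 | 0.03 × 5 = +0.15 |
| 5% | 8 | 3 | 0.05 × 5 = +0.25 |
| 5% | 8 | 8 | 0.05 × 0 = 0 |
| 5% | 8 | 12 | 0.05 × (−4) = −0.20 |

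The last two rows show that the sign depends on when deaths occur. With mortality falling from 10% to 5% and Ld = 3, the control mean is 0.90 × 8 + 0.10 × 3 = 7.5 days, so +0.25 day is 3.3%.

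**Against sampling error.** With 300 per group and an assumed SD of 6 to 8 days, the standard error of the difference is SD × √(2/300), which is 0.49 to 0.65 day. A shift of 0.25 day is about half a standard error or less.

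**Effect on the tests.** This was simulated with 300 independent patients per group, lognormal stays, 2,000 runs per scenario, no clustering by hospital, and an identical stay distribution for survivors in both groups (mean 8 days).

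| In-hospital mortality, control → pathway | Ld | Mean shift | t-test p < 0.05 | Mann-Whitney p < 0.05 |
|---|---|---|---|---|
| 10% → 10% | 3 | +0.02 | 5.3% | 5.1% |
| 10% → 5% | 3 | +0.25 | 6.6% | 9.5% |
| 10% → 5% | 8 | +0.01 | 5.0% | 4.6% |
| 10% → 5% | 12 | −0.21 | 6.6% | 7.9% |
| 15% → 5% | 3 | +0.50 | 11.8% | 23.0% |

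In the second row nearly all Mann-Whitney rejections point to a longer stay on the pathway. The last row is an extreme case, included to show how the effect grows.

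**The case against.** **It belongs in the analysis plan.** Handling of death in a secondary stay variable is often settled in an SAP, and none is shown. A protocol silent on both definition and test could not be faulted. This one names the unit and the tests, and those two choices together produce the scoring. An SAP could still add a rule for death. It could not easily supply a data item that was never collected: Section 5.1.4 has CTcue controls retrieved anonymously according to the defined parameters and endpoints, and in-hospital death is not listed as one.

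**The hazard ratio in Section 5.5 may cover it.** It is tied to no endpoint, so a time-to-event analysis of stay is not excluded. But a hazard ratio that counted any end of stay as the event would have the same flaw.

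**Days regardless of vital status is a legitimate measure.** For resource use and cost this is right, and raw days should be kept for that purpose. It does not serve where a shorter stay is read as a benefit to patients. Reporting 30-day mortality alongside lets a reader suspect the problem but leaves the comparison uncorrected.

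**The effect may be negligible.** Much of this stands. Every rate used is assumed, and the shifts are below one standard error.

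A reader might infer that HOSP-LOS is biased against the pathway whenever it saves lives. The documents do not support that: they say nothing about when deaths occur, and the sign changes with timing. Nor does the protocol firmly predict lower mortality; Section 2 puts satisfaction and ED-LOS first and mentions stay and mortality only as possible consequences.

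**Conclusion.** The point holds in a limited form. As written, the HOSP-LOS comparison treats an in-hospital death earlier than survivors' usual stay as a favourable short stay. It is distorted only if early in-hospital mortality differs between the control and pathway periods. The direction is against the pathway if early deaths are averted and in its favour if they rise. There is no distortion in the mean when deaths fall at the survivors' mean stay, and the direction reverses when they fall later.

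The size is about 0.04 to 0.25 day, assuming stays of 8 days in survivors and 3 to 4 days in those who die, with deaths averted in 1 to 5% of patients.

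A reader might arrive at a larger figure. From 8% mortality, averting deaths in 4% of patients who then stay 15 days instead of 4 gives 0.04 × 11 = 0.44 day, or 57% of a 10% reduction in a mean of 7.68 days. That requires mortality to halve and unusually long stays in those saved, neither of which the documents support. The 10% benchmark is the protocol's ED-LOS effect; none is stated for HOSP-LOS.

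ED-LOS, patient satisfaction and the sample size are unaffected. This is a worthwhile refinement, not a serious defect.

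**What to change.** 1. **Data.** Record in-hospital death (yes or no) and the day of death or discharge in both groups, and include them in the CTcue query for controls. Section 5.4.1 lists the duration of admission and 30-day mortality but neither a discharge date nor a death date, so availability must be confirmed.
2. **Analysis.** Define the event as discharge alive. Compare its cumulative incidence with in-hospital death as a competing event, so that a patient who dies is never counted as discharged. If the hazard ratio in Section 5.5 is meant for this endpoint, say so and name the event. Alternatively, keep the planned Mann-Whitney test and give in-hospital deaths the worst rank.
3. **Clustering.** State how hospital is allowed for in whichever method is chosen, since the GEE sentence does not cover either. With five named hospitals and one optional, stratifying by hospital is the simple choice.
4. **Reporting.** Show in-hospital deaths by group beside the result, and keep raw days as a descriptive measure and for the cost evaluation.

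The cost is a few sentences, one model or ranking rule, and one extra data item to confirm in the controls. The result is slightly less readable than a difference in mean days. No clinical procedure changes.

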### **5.1.4 Control group**

For patients included in the study as controls, the same inclusion and exclusion criteria apply.

Controls will not be specifically asked for informed consent, as each participating hospital will sign a form to collect data for control patients prior to implementing the care pathway. Additionally, it is the responsibility of each participating institution to inform their patients on the policies regarding data collection in study settings.

Obtaining the retrospective control-group will be done by CTcue, if possible. CTcue is a search engine in which unstructured data from an Electronic Health Record (EHR) can be easily found by adding specific queries in to the search engine. These data will be retrieved anonymously according to our defined in- and exclusion criteria, study parameters and endpoints. Specialists at the ED will be unaware of the patients functioning as controls during this study, since data for controls will be collected retrospectively. After 30 and 90 days, the research nurse will evaluate complications that occurred after the patient leaves the care pathway.

In the participating hospitals without access to CTcue, control patients will be gathered prospectively. The ED specialist will save the patient-number of eligible patients in the care pathway (before it is implemented). The specialist in charge of the patient is allowed to use patient data for research, without consent when data is anonymised. The specialist may grant this right to a third party, in this case the research team. This exchange of data has to be approved by the involved departments, which will be the department of Internal Medicine, Geriatrics and the Emergency Department.

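### Readmission is a 90-day endpoint, but no 90-day check is timed for pathway patients, and the control group's follow-up is stated in two conflicting ways

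*Protocol*

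**What the plan says.** Five places in the protocol bear on this.

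- **Endpoint list, section 5.4.1.** Readmission is a binary outcome over 90 days: "Readmissions in 90 days (yes/no". Mortality in the same list is at 30 days, and so is the neighbouring item "Revisits in 30 days (yes/no". The 90-day window is therefore specific to readmission.
- **Section 5.3, items 8 and 9 (pathway patients).** Item 8 promises follow-up without a duration: "Each study participant will be followed-up after leaving the care pathway". Item 9 gives the research nurse two tasks. One is to fill the database with the listed parameters and endpoints, with no time stated. The other is "Collecting data for each participant 30 days after leaving the care pathway".
- **Section 5.1.4 (controls).** "After 30 and 90 days, the research nurse will evaluate complications that occurred after the patient leaves the care pathway".
- **Section 1, Summary, control cohort paragraph.** "After 30 days, the research nurse will evaluate complications that occurred after the patient leaves the care pathway".
- **Section 3, Objectives.** "Frequency of readmissions / revisits" is a secondary objective, with no window.

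For the analysis, section 5.5 states that "the categorical data will be analysed by chi-square or Fisher's exact test", and also mentions GEE to allow for clustering by hospital.

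**The concern.** A yes/no outcome over 90 days can be compared between groups only if each patient in both groups is looked at through day 90 in the same way. The protocol writes down a 90-day time point in one place, and that place is the control-group section. If staff carry out the timed tasks as written, events between day 30 and day 90 may be found in controls and missed in pathway patients. The error would favour the pathway and would look like the fall in readmissions that section 2 hypothesises. If staff follow the Summary instead, the 90-day endpoint has no scheduled collection in either group.

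The start of follow-up is a second, smaller defect. Both control statements count from the moment the patient leaves the care pathway. Controls are gathered before the pathway is implemented, so that moment does not exist for them. The endpoint list names no other start date.

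**Working it through.** **1. The passages side by side**

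| Source | Group | Timed check at day 30 | Timed check at day 90 |
|---|---|---|---|
| 5.3 item 9 | Pathway | yes | none written |
| 5.1.4 | Control | yes | yes |
| Summary | Control | yes | none written |
| 5.4.1 endpoint list | Both | needed for mortality and revisits | needed for readmission |

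- Reading A (5.1.4 with 5.3): controls have a scheduled 90-day check and pathway patients do not. Ascertainment is unequal.
- Reading B (Summary with 5.3): neither group has a scheduled 90-day check. There is no difference between groups, but the endpoint as defined has no planned collection.

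The timed checks do not deliver the endpoint equally in both groups on either reading.

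**2. The plan's own figure**

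The only computed figure in the protocol is the sample size in section 5.1.5, which concerns ED length of stay. It is reproduced here only to fix the group sizes used below. The difference is 10% of 200 min = 20 min, and the SD is read as 1 h 17 min = 77 min:

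n per group = 2 × (1.960 + 0.842)² × 77² / 20² = 2 × 7.849 × 5929 / 400 ≈ 232.7, rounded up to 233, or 466 in total.

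This matches the protocol. (Reading the SD as 1.17 decimal hours gives 194 per group, which does not match.) The stated target is 300 per group. Readmission does not enter this calculation.

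**3. Possible size under Reading A**

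The protocol gives no readmission rate and no timing of readmissions. Both are assumptions here:

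- P = true 90-day readmission risk, the same in both groups: 15% to 35%.
- s = share of 90-day readmissions that occur by day 30: 40% to 80%.

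Controls are observed to day 90 and show P. Pathway patients are observed to day 30 and show P × s. Then

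spurious difference = P × (1 − s), and spurious risk ratio = s.

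The chance that an unadjusted two-sided test at 0.05 declares a difference, although none exists, is approximately

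Φ{ [d√n − 1.96√(2p̄(1−p̄))] / √(p₁(1−p₁) + p₂(1−p₂)) },

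where p₁ = P, p₂ = P × s, d = p₁ − p₂, and p̄ is their mean. This ignores clustering by hospital.

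| P | s | Control vs pathway, observed | Difference (points) | Chance of rejection, n = 233 | n = 300 |
|---|---|---|---|---|---|
| 15% | 80% | 15% vs 12% | 3 | 16% | 19% |
| 20% | 50% | 20% vs 10% | 10 | 86% | 93% |
| 35% | 40% | 35% vs 14% | 21 | over 99% | over 99% |

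Middle row written out for n = 233: d√n = 0.10 × 15.264 = 1.526; 1.96 × √(2 × 0.15 × 0.85) = 0.990; denominator = √(0.16 + 0.09) = 0.5; Φ(0.537 / 0.5) = Φ(1.07) ≈ 0.86.

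Over this range the spurious difference is 3 to 21 points, and the false-positive rate is 16% or more against a nominal 5%. Under Reading B, or with equal 90-day ascertainment in both groups, the spurious difference is 0.

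**The case against.** The best defence is that the text permits a correct conduct of the study.

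- Item 9 of section 5.3 also contains the untimed task of filling the database with the listed endpoints, and that list includes 90-day readmission. A reader might infer that pathway patients are followed only to day 30. The document does not say that; it says that no 90-day time point is written for them. This part of the objection stands.
- The 30-and-90-day sentence in 5.1.4 sits in the control section but speaks of patients leaving the pathway, so it may have been meant for both groups. Both control statements also speak of complications rather than readmissions. Unequal follow-up is therefore one reading and not an established fact. This stands too, but it does not remove the conflict with the Summary or the lack of a 90-day time point in 5.3.
- A reader might put the bias higher by assuming a constant readmission rate. With 30-day risks of 10%, 15% and 20%, 1 − (1 − p)³ gives 27%, 39% and 49% at day 90, a gap of 17 to 29 points. That fixes the share of events by day 30 at 37-41% (for example 0.10 / 0.271), at or near the bottom of the range used above, and nothing in the protocol supports it.
- A reader might also infer that anonymous CTcue retrieval cuts controls off from later events. The protocol describes this retrieval as retrospective and as following the defined endpoints. It nowhere says that the extraction precedes day 90, and section 7.1 provides for a code list. That inference is not supported.
- The exact start of a window is often left to the SAP, which is not at hand. That is fair in general. Here the protocol itself has worded a start that cannot apply to controls, and an SAP cannot restore events that nobody was scheduled to collect.

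**Conclusion.** The point holds as an internal inconsistency that should be corrected. The protocol defines a 90-day readmission endpoint, times data collection for pathway patients at 30 days only, and gives two different schedules for controls. As written, 90-day readmission either has a scheduled check in controls alone or in neither group, and the stated start of follow-up has no meaning for controls.

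If the unequal schedule were carried out, the bias would favour the pathway. Its size cannot be derived from the protocol; the 3 to 21 points rest wholly on the assumed risks and timing. It would arise only if staff completed the 90-day item for pathway patients from 30-day information. Leaving the item blank would instead produce missing data that could be seen.

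The consequence is limited to a secondary objective. Section 5.4.1 places readmission in one undivided list under a main-endpoint heading, but section 3 classes it as secondary. The ED length-of-stay comparison and the 466 patients are not touched.

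**What to change.** Reconcile the Summary, section 5.1.4, section 5.3 (items 8 and 9) and the endpoint list in 5.4.1 so that they say one thing:

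- Both groups are ascertained at 30 and at 90 days, from the same hospital record source and by the same method.
- Each endpoint has one start date, defined identically in both groups and without reference to leaving the pathway. One workable choice is ED arrival for 30-day mortality, and discharge from the index ED visit or admission for revisits and readmissions. Counting readmission from ED arrival is less suitable: eligible patients have an indication for admission, so the index stay would use up part of the window, and the length of that stay is itself an outcome that the pathway may change.
- The 90-day check names readmission explicitly, and not only complications.

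The cost is a wording change and one additional record check per pathway patient, about 300 checks at the target size. If controls have been run on the Summary's schedule, they need the same check. The sample size does not change.
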